### Ethical issues

The trial will be performed according to the Declaration of Helsinki. The study protocol was approved by the Commission for Impact Assessment Research and Ethics, Carl von Ossietzky University, Oldenburg, Germany (Drs. 59/2014). Informed consent will be obtained and validated using both the physician’s and patient’s signatures. Participation is voluntary, and patients can quit the trial at any time without disclosure of their motives for withdrawal and without fear of subsequently receiving poor medical care. In the case of withdrawal, relevant data will be deleted if desired by the patient. Patient names and all other confidential information are subject to medical confidentiality under the German Data Protection Act. Transmission of data will be done in an encrypted format. Others not involved in the trial will have no access to original documents.

## Discussion

The absolute number of patients with pancreatic cancer is increasing, and patients with pancreatic cancer generally have a poor prognosis, so the QOL of patients with pancreatic cancer is of clinical and scientific interest. The complexity of the molecular biology underlying pancreatic cancer makes a breakthrough in the treatment options in the near future highly unlikely. For this reason, and because the rates of traditional outcome parameters such as progression-free survival and overall survival are low, it is very important to develop concepts to improve the QOL of patients with pancreatic cancer in their remaining lives [10]. There are indications that an improved QOL is associated with an improved overall survival rate [10].

As mentioned above, intensified physical training has been shown in particular to measurably increase QOL and reduce the fatigue level of patients with cancer [5, 6]. There are only a few studies that have dealt with the issue of QOL and developing concepts to improve the QOL of patients after pancreatic resection. Yeo et al. described a benefit for patients with resected pancreatic and periampullary cancer from taking part in a home walking program based on the Every Step Counts graduated walking program [5]. They found significant improvements in fatigue levels, physical functioning, and health-related QOL [5]. We believe that our patients will profit from muscle force exercises in addition to endurance exercises. For this reason, we combine a modified version of the Every Step Counts graduated walking program with muscle force exercises. Furthermore, we use the general questionnaire SF-8 as well as the disease-specific questionnaires EORTC QLQ-C30 and QLQ-PAN26 to evaluate the QOL of our patients.

The aim of this study is to investigate whether intensive physiotherapy, consisting of a combination of endurance and muscle force exercises, improves the QOL of patients after pancreatic resection for pancreatic cancer, distal bile duct carcinoma, neuroendocrine tumor, periampullary carcinoma, duodenal carcinoma, or intraductal papillary mucinous neoplasm.

Our hypothesis is that, with the exception of tumor recurrence, QOL should increase more for the intervention group than for the control group, regardless of the reason for surgery, if the type of physical therapy really has an impact on QOL. To be considered clinically relevant, this should be visible even in the heterogeneous study groups employed here.

The main objective criterion is a potential improvement in QOL in the intervention group after intensified physiotherapy 12 months postoperatively as measured by the SF-8 and the EORTC QLQ-C30/QLQ-PAN-26 questionnaires. This pilot study should help us to find an outlined definition of improvement, which may then be implemented in a larger (multicenter) study with appropriate statistical power.

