**Methods/design:**

The proposed trial is a randomized controlled intervention study. After pancreatic resection, the intervention group (cohort A, *n* = 30 patients) will take part in an intensified physiotherapy program consisting of endurance and muscle force exercises. The control group (cohort B, *n* = 30 patients) will take part in standard physiotherapy. Both groups will receive dietary counseling and, if necessary, substitution for endocrine/exocrine pancreatic insufficiency. Quality of life will be evaluated using the Short Form-8 Health Survey and the European Organization for Research and Treatment of Cancer QLQ-C30/QLQ-PAN26 questionnaires.

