**Discussion:**

The aim of this study is to investigate whether intensive physiotherapy improves the quality of life of patients after pancreatic resection. If the results for the intervention group are positive, a multicenter study should be performed with appropriate statistical power. The progressive postresection program includes a structured follow-up after pancreatic resection. In this study, all patients will undergo abdominal computed tomography for follow-up 6 and 12 months postoperatively.

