### Study objectives

The primary aim of this study is the assessment of QOL in the intervention group after intensified physiotherapy 12 months postoperatively, using the SF-8 and the disease-specific EORTC QLQ-C30/QLQ-PAN26 questionnaires in the validated German translations. The longitudinal development of QOL will be measured using the SF-8 and the QLQ-C30/PAN26 questionnaires. The different domains of the questionnaires will be evaluated separately.

The secondary aims of this study include assessment of study dropouts, assessment of physical performance using the Short Physical Performance Battery and ergometry, and assessment of nutritional status using metabolic blood levels and the seven-site skinfold method. If possible, influence on 1-year survival rate, effects of potential adjuvant therapy on QOL, and tumor recurrence rate after 6 and 12 months will be investigated as well. This depends on the actual number of patients and the heterogeneity of the two study groups.

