### Statistical methods

Data analysis will include intention-to-treat and per-protocol analyses. The QOL of patients evaluated with the SF-8 and EORTC QLQ-C3/QLQ-PAN26 questionnaires will be illustrated in histograms. We will evaluate the QOL using the following schedule: 2 days preoperatively and 5 days and 3, 6, and 12 months postoperatively. Furthermore, the course of QOL will be evaluated with a longitudinal regression model.

A multiple linear regression model that includes the following covariates will be used: type of surgery (distal pancreatectomy, pancreaticoduodenectomy, total pancreatectomy), cancer (yes or no), age, BMI, mobility, type of physiotherapy (intensified or standard). We will also perform a covariate analysis.

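### The primary aim and main criterion describe quality of life within the intervention group, whereas the hypothesis and the randomised design call for the 12-month difference between arms

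*Protocol article*

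**What the plan says.** The trial has two arms of 30: "The proposed trial is a randomized controlled intervention study" (Abstract, Methods/design).

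Three places word the objective or the decision in terms of one arm:

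- Study objectives: "The primary aim of this study is the assessment of QOL in the intervention group after intensified physiotherapy 12 months postoperatively".
- Discussion, closing paragraph: "The main objective criterion is a potential improvement in QOL in the intervention group after intensified physiotherapy 12 months postoperatively".
- Abstract, Discussion: "If the results for the intervention group are positive, a multicenter study should be performed with appropriate statistical power".

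The hypothesis, also in the Discussion, is comparative. Leaving tumour recurrence aside, "QOL should increase more for the intervention group than for the control group".

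Statistical methods names intention-to-treat and per-protocol analyses and two models. For the first, "the course of QOL will be evaluated with a longitudinal regression model", and no terms are listed. For the second, "A multiple linear regression model that includes the following covariates will be used": type of surgery, cancer, age, BMI, mobility and type of physiotherapy. The visit that supplies the outcome of the second model is not given. QOL is measured at five visits: 2 days before surgery, then 5 days and 3, 6 and 12 months after it.

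**The concern.** A change in QOL within the intervention arm mixes the effect of physiotherapy with everything else that happens in the year after resection: surgical recovery, adjuvant treatment, recurrence, and loss of the sickest patients from follow-up. The control arm was randomised to separate these. A criterion that leaves it out can be met when physiotherapy does nothing, and can be missed when physiotherapy helps but the general course is downward.

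Two uses of the result depend on the wording. The Abstract makes the larger trial conditional on the intervention group's results. The Discussion also says that the pilot is to help define improvement for that trial, so a one-arm definition of success could be carried forward into it.

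**Working it through.** **The plan's own figures.** There is nothing to reproduce. Sample size considerations states that no calculation was done, and the article gives no alpha, power, effect size or SD. The arm sizes agree: 30 + 30 = 60.

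**The statements side by side.**

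| Place | Quantity | Comparator named |
|---|---|---|
| Study objectives, primary aim | QOL in the intervention group at 12 months | No |
| Discussion, main criterion | Improvement in QOL in the intervention group at 12 months | No |
| Abstract, go decision | Results for the intervention group | No |
| Discussion, hypothesis | Larger increase than in the control group | Yes |
| Statistical methods, listed regression | Contains type of physiotherapy | Yes, through the arm term |

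Write g for the mean change common to both arms and D for the effect of physiotherapy at 12 months. The within-arm criterion looks at g + D. The hypothesis concerns (g + D) − g = D. The two agree only if g = 0, and nothing in the article supports that.

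**Illustration of what g can do.** All inputs except n = 30 are assumptions: a two-sided 5% test of mean change, all 30 patients observed at 12 months, and a correlation of 0.5 between the preoperative and 12-month scores. The SD of the change is then √(2 × (1 − 0.5)) = 1 SD of the score, and the standard error is √(1/30) = 0.183. The chance of a significant improvement is 1 − Φ(1.96 − (g + D)/0.183).

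| Common change g (SD) | Physiotherapy effect D (SD) | Chance that improvement is shown |
|---|---|---|
| 0.2 | 0 | 19% |
| 0.3 | 0 | 38% |
| 0.5 | 0 | 78% |
| 0 | 0.5 | 78% |
| −0.3 | 0.5 | 19% |
| −0.5 | 0.5 | 2.5% |

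With a one-sample t test in place of the normal approximation, the second and third rows become 36% and 75%. The pattern does not depend on the method: the same 78% arises with no effect and with an effect of 0.5 SD.

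**The models.** If the listed regression is fitted to the 12-month scores, its arm coefficient is the adjusted 12-month difference between arms. It needs no visit or arm-by-visit term for that.

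Only if the same list were the full specification for all five visits would a single arm term average over visits. With equal correlation between visits, that average is the plain mean of the five true differences:

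- Effect growing linearly with months (day 5 taken as 0.2 months): (0 + 0.017 + 0.25 + 0.5 + 1)/5 = 0.35 of the 12-month difference.
- Full effect from month 3: (0 + 0 + 1 + 1 + 1)/5 = 0.60.
- Effect only at month 12: (0 + 0 + 0 + 0 + 1)/5 = 0.20.

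With a first-order autoregressive correlation of 0.3 to 0.7, the same three cases give 0.38 to 0.42, 0.55 to 0.59 and 0.24 to 0.35. The overall range is 0.20 to 0.60, and it applies only under that reading.

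**The case against.** The strongest reply is that the comparison is plainly intended and the wording merely loose. The hypothesis is comparative, the trial is randomised, the listed regression contains the arm, and intention to treat is planned. Design and trial flow makes the follow-on trial depend on positive results of the study, without singling out an arm. The trial is also a pilot with feasibility among its aims, so no confirmatory claim or sample size hangs on the sentence. This stands as far as it goes: the authors very likely mean to compare. It does not remove the conflict, because the one-arm form appears in the primary aim, the main criterion and the Abstract's go decision, which are the statements against which the result will be judged.

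A reader might also infer more than the article supports:

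- *That the control group is not used.* The hypothesis and the arm term in the regression contradict this. What is missing is the comparator in the aim and the criterion.
- *That the models cannot give the 12-month difference because no visit or arm-by-visit term is listed.* The listed regression can, if fitted to the 12-month scores. The terms of the longitudinal model are not listed, and an article may leave them to the full protocol or analysis plan.
- *That the false-positive rates or the dilution factors describe this trial.* They rest on a within-arm test and a pooled five-visit fit that the article never states.

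**Conclusion.** The point holds for the objective, and it should be corrected. The primary aim, the main criterion and the Abstract's go decision leave out the comparator that the hypothesis requires. Read literally, a change shared by both arms could decide the result in either direction. This is a misstated target of estimation that the article itself contradicts. It is not a missing detail, and it is not an error in the sample size.

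That conclusion rests on the text alone. Its numerical size cannot be fixed from the article. The illustrative 38% to 78% for a shared improvement of 0.3 to 0.5 SD, and the 19% for a real 0.5 SD benefit against a 0.3 SD decline, depend on the assumed test, correlation and complete follow-up.

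On the models, only a conditional remark is warranted: neither is tied to the 12-month contrast between arms, and averaging over visits would matter only if the covariate list also governs the five-visit model.

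**What to change.** 1. In Study objectives and in the closing paragraph of the Discussion, restate the primary aim and main criterion as the difference between arms (intensified minus standard) in QOL at 12 months, in the intention-to-treat population.
2. In the Abstract, make the follow-on trial conditional on a between-group difference in favour of intensified physiotherapy.
3. In Statistical methods, say which coefficient estimates that difference. Either of two choices will do: the arm coefficient from a regression on the 12-month score, or the 12-month contrast between arms from the longitudinal model. In both, adjust for the preoperative score of the same QOL scale, which is already collected but is not in the covariate list.
4. If the covariate list is also meant for the five-visit longitudinal model, add visit and arm-by-visit terms, so that the arm effect is not averaged over the preoperative and day-5 visits.
5. Report within-arm changes descriptively.

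The cost is wording and analysis. No new data, visits or patients are needed, and the article places the first enrolment in the future, so at that point the change could be made before any outcome was seen. The downside is that the result may look less favourable than an improvement within one arm.

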### Trial status

Enrollment of the first patient is planned for February 2016.

## Abbreviations

BMI: body mass index
CA 19-9: cancer antigen 19-9
CEA: carcinoembryonic antigen
CT: computed tomography
EORTC: European Organization for Research and Treatment of Cancer
Hb: hemoglobin
HbA1c: glycated hemoglobin A1c
HDL: high-density lipoprotein
LDL: low-density lipoprotein
QOL: quality of life
SF-8: Short Form-8 Health Survey
SF-36: Short Form-36 Health Survey
TTE: transthoracic echocardiography
